### The interventions

#### The functional training group (experimental group)

The patients who are allocated to the experimental group are receiving a functional training program initiated by the nurses in addition to the usual physiotherapy. The present functional training program is based on transfer activities of daily life, tailored to meet each individual’s needs. It is targeted to the level of difficulty relevant for each participant. The functional training program is performed approximately 4 times a day, 7 days a week during the short-term stay of 2–3 weeks. The nurses will be educated, motivated, guided, and frequently supervised by the research physiotherapists.

The functional training program is inspired by prior research on the effect of a walking skill training program based on ambulatory activities and transfers in patients with total knee [27] and total hip [28] arthroplasty. These patients changed statistically significantly more in walking capacity measured by the 6-min’ walk test, compared to controls. The program is also inspired by the gait and balance program developed by Thingstad et al [29] and performed in patients 4 months after the hip fracture.

The content of the present functional training program is as follows:
*Stepping.* Standing with support, weight transfer without stepping. Progression: Short steps forward and sideways, less support, several repetitions in series of 3.
*Walking in the corridor with a walking aid.* Walk several short distances. Rest on a chair if necessary. Progression: Walk with longer steps, good stride, higher speed, start, stop, and turns. Walk in the corridor as long as you are able to.
*Step-up.* Tapping on to the step but not stepping up. With support: stepping up one or several steps. Progression: Climb up and down the staircase.
*Chair rise.* Raising/lowering on heightened chair with arm support. Progression: Raising/lowering on normal chair with less or without arm support, several repetitions in series of 3.
*Squats.* Stand with arm support. Bend your knees by lowering the body. Progression: Less arm support, deeper bends, several repetitions in series of 3.
*Heel lift.* Stand with arm support. Several repetitions in series of 3.

When transferred to home, the patients are encouraged to continue their exercises at minimum twice daily. They are given a written exercise program with progression before discharge from the nursing homes.

#### The control group

The patients who are allocated to the control group are receiving treatment as usual; physiotherapy 2–3 times a week during their short-term stays.

### Measures

Assessments will be performed before discharge from hospital (baseline), when the patients have stayed at the nursing home for 2 weeks, and at 3 and 12 months after surgery (Table 1). The 3- and 12-month assessments will be performed at Bærum Hospital or in the patient’s home if necessary. Blinded assessors (experienced physiotherapists) will perform the assessments. Before the study is initiated, the testers are taking part in a training program regarding testing procedures in order to ensure high inter-rater test reliability.

**Table 1 Tab1:** Data collection at different time points in the HIPFRAC study

	4-5 days after surgery	3 weeks after surgery	3 months after surgery	1 year after surgery
*Personal variables*				
Age	x			
Sex	x			
Education	x			
Cohabiting status	x			
Comorbidity	x			
Type of operation	x			
History of falls	x			
Minimal mental status evaluation (MMS-E)	x			
*Performance-based measures*				
Short Physical Performance Scale (SPPB)	x	x	x	x
ActivePAL		x		
Timed Up & Go (TUG)	x	x	x	x
Grip strength	x			x
*Self-reported measures*				
New mobility score (NMS)	x (recalled from prefracture)			^X^
Walking habits	x (recalled from prefracture)		x	x
Health-related quality of life (EQ-5D-5 L)	x	x	x	x
Pain at rest and while walking	x	x	x	x
University of California Los Angeles (UCLA) activity scale	x	x	x	x
Fall efficacy scale (FES)	x	x	x	x

#### Primary outcome of physical functioning

*Short physical performance battery (SPPB)* is a measure of physical functioning [30]. SPPB evaluates balance, mobility and muscle strength by examining an individual’s ability to stand in different positions, time to walk 4 m, and time to rise up from and sit down on a chair 5 times [30]. The tests are scored between 0 and 4, leaving a maximum score of 12 [30]. The SPPB will be applied before discharge from hospital, after 14 days in the nursing home, and 3 and 12 months after surgery.

### Secondary outcomes

#### Performance -based measures of physical functioning

*Timed Up &Go (TUG)* is a measure of mobility. The patient gets up from a chair with armrest, walks forward for three meters, turns, walks back and sits down in the chair [31, 32]. The time is recorded in seconds and measured before discharge from hospital, after 14 days in the nursing home, and at 3 and 12 months after surgery.

In the *stair climbing test* the patients ascend and descend eight steps with a step height of 16 cm with alternate legs while holding onto the rail. The time is recorded in seconds and the test will only be recorded at 3 and 12 months.

*Single-axis accelerometers (activPAL)* assess the patients’ physical behavior during short-term stays in the nursing homes. The accelerometer is attached to the patients’ non-affected thigh before discharge from hospital. Mean upright time and mean upright events during the first week in the nursing homes are measured. The nurses remove the devices after 14 days.

*A hand dynamometer* is used to measure grip strength before discharge from hospital and at 12 months. The grip strength is associated with general muscle strength and walking recovery, and it might provide important prognostic information regarding the patients’ future functional trajectory [33].

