## Background

Hip fracture (a fracture of the upper part of the femur), is a worldwide health problem in old age [1, 2]. World-wide, there are approximately 1.7 million hip fractures each year. The highest rates are seen in North America and Europe [1]. In Norway (with 4.7 million inhabitants), about 9000 patients are hospitalized and operated for hip fractures annually. This is among the highest reported hip fracture incidence rates in the world [1–3], even though the hip fracture rates in Norway have declined during the past 15 years. Nevertheless, the forecasted growing number of older people might cause an increase in the absolute number of fractures. This may lead to a substantial, societal, economic and public health burden [4]. Hip fracture is a serious event; one out of every four patients die within one year. Survivors often report severe pain and loss of physical functioning [3].

In a systematic review it was estimated that 42% of survivors after hip fracture did not return to their pre-fracture level of physical functioning, and 35% became incapable of walking independently after the fracture [5]. Moreover, 50% of those able to walk without a walking device before the fracture became permanently dependent on a walking device, and 50% of survivors had persistent loss of independence in daily activities after the fracture [6, 7]. Long-lasting mobility limitations after hip fracture may lead to prolonged physical disability, increased fall risk and new injuries, and 15% of the patients will become permanently institutionalized [7]. Altogether, these impairments cause considerable suffering. Therefore, strategies for hip fracture rehabilitation to enhance the patients’ recovery of physical functioning and prevent future falls is an urgent health care challenge. With such serious consequences, prevention and treatment of fractures to improve outcomes are crucial.

In Norway, the mean length of hospital stay (LOS) after hip fracture surgery is 5–6 days [8]. An increasingly shorter LOS is in line with international studies showing that aging patients are discharged from the hospital “quicker and sicker” [9, 10]. After discharge, most of the patients in Norway are transferred to short-term stays in nursing homes in primary health care before they are able to return to home.

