### Recruitment and study population

Recruitment takes place at Bærum Hospital after hip fracture surgery. Patients with an acute low-energy hip fracture (intracapsular, throchanteric or subtrochanteric) and treated surgically, ≥ 65 years of age, living in their own homes prior to the fracture, and able to give an informed consent, are invited to participate in the study. Patients are excluded if they are unable to walk 10 m with or without a walking aid prior to the fracture, have a score of less than 15 points on Minimal Mental Status Evaluation (MMS-E) in the acute phase, have a pathological fracture, life expectancies of less than 3 months, medical contraindications for training, or are incapable of understanding and speaking Norwegian.

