### Data analysis and statistical power

The sample size is calculated from a small meaningful change in SPPB, the primary outcome measure [43]. A small meaningful change in the SPPB is mean (SD) 0.5 (1.48) points [44]. With a significance level of 0.05 and power of 80% this estimate requires 140 patients, 70 patients in each group. To compensate for potential drop-outs at least 160 patients will be included in the study. All data will be stored at the research server at the hospital. Between-group differences in normal distributed continuous variables will be analyzed with *t*-tests and/or analysis of covariance (ANCOVA) according to the principle of intention-to-treat (ITT). Missing data will be imputed by carrying the last value forward. Effect sizes will be calculated. To examine relationships correlation and/or multiple regression analyses will be used [45]. The significant level is set to *p* < 0.05.

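### TUG and stair climbing are recorded only in seconds under a blanket carry-forward rule, so inability to do the test has no proper place in the analysis and can bias these secondary outcomes in either direction

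*Protocol article*

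**What the plan says.** The protocol article, under Performance-based measures of physical functioning, says of TUG: "The time is recorded in seconds and measured before discharge from hospital, after 14 days in the nursing home, and at 3 and 12 months". Of the stair test (eight steps up and down) it says: "The time is recorded in seconds and the test will only be recorded at 3 and 12 months". Neither description gives a worst value or a code for a patient who cannot do the test.

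Under Data analysis and statistical power, "Between-group differences in normal distributed continuous variables will be analyzed with" t-tests and/or ANCOVA, on the intention-to-treat principle. The same paragraph says: "Missing data will be imputed by carrying the last value forward". No outcome and no reason for absence is exempted.

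The primary outcome is built differently. Each SPPB test is scored from 0 to 4, so the scale has a floor.

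**The concern.** Inability to stand up and walk, or to climb stairs, is a known result and the worst one. It is not an unknown value. Recorded only in seconds, it leaves a blank, and the only stated rule for a blank is carry-forward.

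The training is also meant to change who is able. Its listed content runs from shifting weight without stepping, and tapping a step without mounting it, up to using the staircase. Who has a valid time may therefore depend on the arm. At stake is the reading of the timed mobility results, which serve the secondary aim on ambulation.

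**Working it through.** The plan gives no figure for TUG or stair time, so there is nothing to reproduce. The check has four steps.

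**1. Is inability foreseeable from the article?** Yes.
- The walking criterion at entry concerns the time before the fracture: "Patients are excluded if they are unable to walk 10 m with or without a walking aid prior to the fracture". None is stated for after surgery.
- Table 1 places the first TUG at 4-5 days after surgery.
- The programme provides for patients who cannot yet step or climb.
- The stair test requires alternate legs on each of eight steps.
- The Background says of hip-fracture survivors in general that "35% became incapable of walking independently after the fracture". Applied to the planned 160 this would be 0.35 x 160 = 56. That is a loose upper guide from a wider population and not an estimate for this trial.

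**2. What happens to an unable patient under the rule as written?**

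| Test and visit | Earlier time exists | No earlier time |
|---|---|---|
| TUG at 2 weeks in the nursing home, 3 and 12 months | keeps the earlier time although unable | drops out |
| Stairs at 3 months | cannot occur | every unable patient drops out |
| Stairs at 12 months | keeps the 3-month time | drops out |

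**3. Hand illustration (all inputs assumed).** In control 70% are able, with mean 25 s. In training the same 70% average 25 s, and a further 10% become able at 50 s. Training is truly better.
- *Unable patients drop out.* Control mean 25 s. Training mean (0.70 x 25 + 0.10 x 50)/0.80 = 22.5/0.80 = 28.1 s. The difference of +3.1 s counts against training.
- *Every unable patient carries an early time c.* Training: 0.70 x 25 + 0.10 x 50 + 0.20c = 22.5 + 0.20c. Control: 0.70 x 25 + 0.30c = 17.5 + 0.30c. The difference is 5 - 0.10c. At c = 40 s this is +1.0 s, at c = 50 s it is 0, and above 50 s it favours training. The sign rests on a time measured at an earlier visit.

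**4. Simulation (assumed inputs).** 80 patients per arm, median TUG 40 s early and 22 s later, log-SD 0.4, the frailest patients unable at follow-up, underlying times identical in both arms, 1,500 runs. Entries are mean training minus control in seconds; a positive value favours control.

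| Unable: training v control | Unable dropped | Carry-forward, all unable have an early time | Carry-forward, none has |
|---|---|---|---|
| 10% v 10% | about 0 | about 0 | about 0 |
| 10% v 20% | +1.1 | -2.6 | +1.0 |
| 10% v 30% | +2.0 | -4.8 | +2.0 |
| 20% v 40% | +1.8 | -4.5 | +1.8 |

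In the last three rows the only true difference is fewer unable patients under training. The sign turns on whether those patients happened to have an early time. Even the negative values do not measure the benefit, because they mix early post-operative times with later ones.

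**The case against.** The strongest reply is that the article nowhere says inability is coded as missing. Coding of non-completers often sits on the case report form or in the analysis plan. That is fair: the step from a blank time to carry-forward is an inference. It is the natural one, because the article gives no other coding and its missing-data sentence allows no exception. That sentence is a stated choice, not a detail left out.

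The article also limits t-tests and ANCOVA to normally distributed variables and does not say that TUG or stair time will be treated as such. A rank method or transformation is not excluded. But neither helps if the unable patient enters with an old time or not at all.

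A reader might infer four stronger things, which the document does not support:
- *That the analysis compares only the able.* It does not. Carry-forward keeps some unable patients in, with a finite time.
- *That the carried time is generally too good.* It is better only than being unable. The first TUG is 4-5 days after surgery, so in recovering patients who are absent for other reasons a carried time will usually be slower than the true one.
- *That the results will be biased, and against training.* Bias between arms needs inability to differ by arm, and its sign is not fixed. The 28.1 s v 25 s example tests dropping patients, not carrying values forward.
- *That some 56 patients will lack a time.* The 35% concerns independent walking among survivors in general. Walking with an aid may still allow a TUG, and the trial restricts entry.

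**Conclusion.** The point holds in a limited form. As written, the plan has no place for inability on TUG or stairs other than an outdated finite time or loss from the comparison. On the stair test at 3 months, loss is the only possibility. If inability differs between arms, these comparisons can shift either way: from -4.8 s to +2.0 s in the simulated cases, and by about 0 when inability was equal.

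Those sizes rest wholly on assumed times and assumed proportions unable. The article gives no data from which to estimate either, so the real size is unknown. The conclusion also assumes that no other document codes inability separately.

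The affected outcomes are secondary. SPPB is scored from 0 and does not share this particular problem, although carry-forward still applies to SPPB values that are missing for other reasons. This is a modest point that is worth correcting.

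**What to change.** Add to the analysis section that a patient who cannot do TUG or the stair test is recorded as unable, that this is an outcome and not missing data, and that carry-forward does not apply to it. Then:
- put a reason-not-done code on the form for each timed test;
- report the proportion able by arm and visit for both tests;
- compare arms with unable as the worst value, either as speed (the reciprocal of time, unable = 0) or by a rank test with unable in the lowest rank;
- treat only tests not done for other reasons as missing.

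The cost is a sentence or two in the analysis section and one field on the form. The downside is that the result is no longer purely a mean difference in seconds; that can still be reported descriptively among those able. The change should not be sold as a gain in power. In the simulation the rank test gave p < 0.05 in 25-26% of runs at 10% v 30% unable, against 28-30% for a t-test with unable patients dropped. But the mean difference in that t-test pointed the wrong way. The gain is that regained ability counts as a benefit.

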#### Self- reported measures of physical functioning, physical activity and quality of life

*New mobility scale (NMS)* measures pre-fracture physical functioning. The NMS classifies the pre-fracture physical functioning as either low (from 2–6) or high (from 7–9) [34]. It is used only in the acute phase while the patients are in hospital.

*Walking Habits questionnaire* measures the frequency and duration of the patient’s weekly walking habits pre-fracture and at three and 12 months after surgery [35, 36].

*Fall Efficacy Scale (FES)* measures the patient’s fear of falling [37, 38]. Sixteen questions are scored on a 4-point scale ranging from “not at all concerned” to “very concerned” about falling on pre-fracture level and at 3 and 12 months.

*The University of California, Los Angeles (UCLA) Activity Scale* measures the patients’ level of physical activity [39]. The patient’s physical activity is evaluated on a 10-point scale based on 10 descriptive activity levels ranging from wholly inactive and dependent to regular participation in impact sports. Pre-fracture-, 3- and 12-month activity level will be measured.

*Health and Quality of Life Questionnaire (EQ-5D-5 L)* measures the patient’s health-related quality of life [40, 41]. Five questions are scored on a 5-point scale. Additionally, the self-rated health is reported on a vertical, visual analogue scale. Cost-qualy analysis will be provided from EQ-5D-5 L. The measures will be taken before discharge from hospital, after 14 days in the nursing home, and at 3 and 12 months after surgery.

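### Carrying the last value forward gives a patient with no post-fracture Walking Habits answer the recalled level from before the injury, and so a score of no loss

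*Protocol article*

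**What the plan says.** Under Data analysis and statistical power, the protocol article gives its whole missing-data rule in one sentence: "Missing data will be imputed by carrying the last value forward". It exempts no outcome, no visit and no death.

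The section on self-reported measures says that Walking Habits "measures the frequency and duration of the patient’s weekly walking habits pre-fracture and at three and 12 months after surgery". Table 1 (Measures) agrees: the hospital entry is marked "x (recalled from prefracture)", the 3-week cell is empty, and the next marks are at 3 months and 1 year.

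For three other questionnaires the text and Table 1 differ:

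- **UCLA.** The text says "Pre-fracture-, 3- and 12-month activity level will be measured". Table 1 marks all four time points, including 3 weeks, and does not label the first as recalled.
- **FES.** The text has it scored "about falling on pre-fracture level and at 3 and 12 months". Table 1 again marks all four time points without a recall label.
- **NMS.** The text says "It is used only in the acute phase while the patients are in hospital". Table 1 has a recalled pre-fracture entry and a further mark at 1 year.

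EQ-5D-5L has an in-hospital baseline and is not described as pre-fracture: "The measures will be taken before discharge from hospital, after 14 days in the nursing home, and at 3 and 12 months after surgery". SPPB and TUG are likewise first measured in hospital.

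**The concern.** Carrying a value forward is usually criticised after surgery because it freezes an early, low score. Here the error runs the other way. The carried value predates the injury whose consequences the questionnaire is meant to record, so a patient who could not be followed up looks better than one who was seen with a real loss.

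Physical activity and fear of falling are among the declared secondary aims. For any instrument with this schedule, average loss would be understated and a real treatment effect diluted. If the arms differ in missing follow-up, the arm with more of it would be favoured. One rule would also bias the trial's outcomes in opposite directions, depending on whether an instrument's first value is post-operative or pre-fracture. A reader who accepted the rule as cautious for SPPB could easily miss this.

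**Working it through.** **Step 1. Trace the rule through each schedule.**

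| Instrument | Schedule used | Missing pattern | Value filled in |
|---|---|---|---|
| Walking Habits | text and Table 1 agree | 3 months only | pre-fracture, at 3 months |
| Walking Habits | same | 3 and 12 months | pre-fracture, at both |
| Walking Habits | same | 12 months only | 3-month value (post-fracture) |
| UCLA, FES | text | as for Walking Habits | as for Walking Habits |
| UCLA, FES | Table 1 | 3 months | 3-week value where obtained; pre-fracture only if that is missing too and the first entry is a pre-fracture one |
| NMS | text | no follow-up planned | nothing to fill |
| NMS | Table 1 | 1 year | always pre-fracture |

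**Step 2. Invented Walking Habits records.** All three patients walked daily before the fracture.

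- Patient 1 is seen at 3 months walking once a week: scored as a loss.
- Patient 2 is seen at neither 3 nor 12 months: scored as walking daily at both, no loss.
- Patient 3 is seen at 3 months walking once a week and misses 12 months: scored as once a week at 12 months. This is ordinary carry-forward, not the present defect.

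**Step 3. Size.** The plan gives no expected loss, SD or missingness for these scales, so the result is stated in symbols. Let D be the true mean loss from the pre-fracture level in the control arm, with loss taken as change for the worse (for FES, more concern). Let d be the true benefit of the experimental arm. Let mE and mC be the shares with no post-fracture value by the visit in question. Assume that patients not seen have the same mean loss as those seen in their arm.

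- Control mean change after filling: −D(1 − mC). The loss is understated by mC × D.
- Experimental mean change after filling: −(D − d)(1 − mE).
- Difference: d(1 − mE) + (mE − mC)D.

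*Equal missingness, m in both arms:* the difference is d(1 − m).

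- m = 12.5%: factor 0.875, so a true difference of 0.5 becomes 0.5 × 0.875 = 0.44.
- m = 25% (assumed): factor 0.75, so 0.5 becomes 0.375.

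*Unequal missingness, no true effect (d = 0):* the difference is (mE − mC)D, in favour of the arm with more missing data. All splits are assumed.

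- 10% v 15%: 0.05 D.
- 10% v 20%: 0.10 D.
- 5% v 20%: 0.15 D.

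**Step 4. What m could be.** The only related figure in the plan is the drop-out allowance: (160 − 140)/160 = 20/160 = 12.5%. It covers all drop-out, whereas m counts only patients with no post-fracture value. Suppose 12.5% are missing at 12 months, nobody returns after dropping out, and 5% to 10% were already missing at 3 months (assumed). Then 0.05/0.125 = 40% to 0.10/0.125 = 80% of the missing 12-month values are filled with the pre-fracture level, so m at 12 months is 5% to 10%. Using 12.5% there is an upper reading of the allowance.

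**The case against.** The strongest case against is that only Walking Habits is affected beyond dispute. On Table 1, UCLA and FES have a 3-week assessment that would normally be the value carried. On the text, NMS has no follow-up at all. This stands: those three are conditional, and the conflicts have to be settled rather than read whichever way creates the defect.

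A reader might infer that every patient with missing data is scored as fully recovered. The schedule does not support that. A patient seen at 3 months carries a post-fracture value to 12 months. No loss also means equality with the patient's own recalled level, not the top of the scale.

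A reader might also take the Background's figure that 42% of survivors do not regain pre-fracture function, and conclude that the share appearing to have returned rises from 58% to 0.58 × 0.875 + 0.125 = 63%. That figure concerns physical functioning in a review, not walking frequency, activity level or fear of falling, and the plan announces no analysis of the share returned. The figure shows only that assuming zero loss is at odds with the protocol's own account of recovery.

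It is fair to add that a false benefit needs unequal missingness, which is assumed here; that follow-up visits may take place at home, which should limit losses; that mortality is recorded separately; and that replacing the carry-forward rule for the whole trial would remove this problem too. An analysis plan might say whether a baseline value may be carried. The sentence as published, however, makes no exception, and for Walking Habits it leads directly to the wrong value. Planning ANCOVA does not help: if the arms are alike in pre-fracture level, adjusting for it leaves the term (mE − mC)D in place.

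**Conclusion.** The point holds for Walking Habits at 3 months, and at 12 months when 3 months is missing too. It holds for UCLA and FES only if the text's schedule is the one followed, and for NMS only if Table 1's 1-year mark stands.

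The mean loss is understated by m × D. A true group difference is multiplied by 1 − m under equal missingness: 0.875 if the whole 12.5% allowance had no post-fracture value, and about 0.90 to 0.95 at 12 months under the assumed drop-out patterns. Unequal missingness adds a false difference of (mE − mC)D, for example 0.10 D at an assumed 10% v 20%. These sizes rest on equal mean loss in seen and unseen patients. If the unseen fare worse, which is plausible in this population, the understatement is larger.

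The documents do not support a claim that the trial's main result is biased by this route: SPPB starts from an in-hospital value. The point concerns secondary outcomes, but the error is built into a stated rule and is cheap to remove.

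**What to change.** Change the missing-data sentence under Data analysis and statistical power so that it says:

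- a recalled pre-fracture value is never carried forward as a post-fracture outcome;
- for Walking Habits, and for UCLA, FES and NMS where they have follow-up, the pre-fracture value enters as a baseline covariate;
- the observed 3- and 12-month values are analysed with a likelihood-based repeated-measures model or with multiple imputation;
- outcomes are not imputed after death, and deaths are reported separately by arm.

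Reconcile Table 1 with the text for UCLA, FES and NMS: which time points are assessed, and whether the first entry is a recalled pre-fracture level or the state in hospital.

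The cost is a few sentences, a corrected table and slightly more analysis work. No new data are needed. Standard errors will be slightly wider, because filled-in values will no longer count as observed.

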#### Secondary aims

To assess the immediate and long-term effects of the same program on ambulation, level of physical activity, health-related quality of life, pain in rest and while walking, fear of falling, number of secondary falls, support from health care services, place of residence, mortality rate, and the cost-effectiveness of the intervention.

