#### Sociodemographic - and other variables

Age, sex, living arrangements, educational level, previous falls, home care services, medication list, date of hip fracture, and type of operation are variables that are collected at baseline. Information about number of falls, readmission to hospital, and mortality are also registered at discharge from the nursing homes, at 3 and 12 months after surgery.

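### The general carry-forward rule makes no exception for death, so, read literally, patients who die keep earning QALYs to 12 months in the planned cost-QALY analysis

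*Protocol article*

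**What the plan says.** Four parts of the protocol article bear on this.

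- **Secondary aims** ends its list with "mortality rate, and the cost-effectiveness of the intervention", so survival and cost-effectiveness are both declared aims.
- **Self-reported measures** says "Cost-qualy analysis will be provided from EQ-5D-5 L" and gives the EQ-5D-5L schedule: "The measures will be taken before discharge from hospital, after 14 days in the nursing home, and at 3 and 12 months after surgery".
- **Data analysis and statistical power** gives the only missing-data rule: "Missing data will be imputed by carrying the last value forward". It names no outcome, sets no limit and does not mention death.
- **Background** says of hip fracture patients in general that "one out of every four patients die within one year". Under **Sociodemographic - and other variables**, "mortality are also registered at discharge from the nursing homes, at 3 and 12 months after surgery"; dates of death are not mentioned.

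The article does not say whether an EQ-5D-5L value absent because of death counts as missing, whether the carry-forward rule governs the economic analysis, or how QALYs are computed after a death.

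**The concern.** A QALY is utility accumulated over time alive. Once a patient has died, the utility is not unknown: it is 0 by definition. This sets EQ-5D-5L apart from the primary outcome. SPPB after death has no defined value, so its handling is a choice of estimand. Utility after death does have one, and carrying a living value forward replaces a known number with a wrong one.

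Under the rule as written, a patient who dies after the 3-month visit enters month 12 with the 3-month utility. One who dies before 3 months keeps an early post-operative value for the rest of the year. Two things follow. Mean QALYs are too high in both arms. And the part of the QALY difference that comes from survival, in whichever direction, largely disappears from the effect side of the cost-effectiveness result.

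**Working it through.** The article states no QALY figure, so there is none to reproduce. The check sizes the effect of the rule.

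**Inputs from the article:** one-year mortality m = 0.25 (Background); EQ-5D-5L at baseline, 3 weeks, 3 months and 12 months (Table 1), taken as t = 0, 3/52, 0.25 and 1 year; at least 160 patients.

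**Assumptions:** constant hazard over the year; constant utility of 0.4 to 0.6, or a recovering profile of 0.30, 0.45, 0.60, 0.70 at the four visits; other mortality levels and between-arm contrasts, for illustration.

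**Step 1. Life-years lost in year 1 per enrolled patient** = 1 − m / (−ln(1 − m)).

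| m | Deaths in 160 | Life-years lost | × 0.4 | × 0.6 |
|---|---|---|---|---|
| 0.10 | 16 | 0.051 | 0.020 | 0.031 |
| 0.15 | 24 | 0.077 | 0.031 | 0.046 |
| 0.20 | 32 | 0.104 | 0.041 | 0.062 |
| 0.25 | 40 | 0.131 | 0.052 | 0.079 |

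For m = 0.25: 1 − 0.25/0.2877 = 0.131. The last two columns are the QALYs wrongly credited per patient when utility is flat. At 25% mortality the relative overstatement is 0.131/0.869, about 15%; at utility 0.6, for example, carry-forward gives 0.600 against a true 0.521.

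**Step 2. Survival-driven difference, flat utility.** Under carry-forward every patient scores the same whether alive or dead, so this part of the difference is exactly 0. The true values are:

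- 25% v 20%: 0.1310 − 0.1037 = 0.0273 years, or 0.011 to 0.016 QALY.
- 25% v 15%: 0.1310 − 0.0770 = 0.0540 years, or 0.022 to 0.032 QALY.

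**Step 3. Recovering profile.** Survival to t is S(t) = (1 − m)^t. Under carry-forward the mean recorded utility at visit j is the previous mean plus (u_j − u_{j−1}) × S(t_j), and QALYs are the trapezoid area.

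- m = 0.25: S = 0.984, 0.931, 0.750. Mean utilities are 0.300, 0.448, 0.587, 0.662. The area is 0.0216 + 0.0995 + 0.4685 = 0.590.
- m = 0.15: S = 0.991, 0.960, 0.850. Mean utilities are 0.300, 0.449, 0.593, 0.678. The area is 0.0216 + 0.1001 + 0.4763 = 0.598.

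The true mean, integrating u(t)S(t) with utility 0 after death, is 0.525 and 0.560 respectively. At 25% mortality the overstatement is 0.590 − 0.525 = 0.065, about 12%. For 25% v 15% the true difference is 0.035 and carry-forward gives 0.009, so about a quarter survives and three quarters is lost.

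**The case against.** **The link is an inference.** The carry-forward sentence follows the one on t-tests and ANCOVA, and that section does not mention QALYs, costs or death. An analyst could fairly hold that a dead patient's utility is known and so never missing, and the article's single sentence on the economic analysis presumably rests on fuller documents not shown. This stands as a limit on certainty: a reader might infer that the trial has decided to credit QALYs to the dead, and the article does not say so. It does not dispose of the point. The rule is the only one given and is unrestricted, and a correct economic analysis would have to depart from its plain wording.

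**The loss is not always total.** A reader might infer that any survival difference vanishes. That holds exactly only for flat utility, which is unlikely when measurement starts days after surgery. Deaths would also still affect the cost side, and mortality is a separate aim, so a mortality difference would not go unreported.

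**The size rests on assumptions.** The 25% is a background figure for a less selected population. The trial excludes patients with "life expectancies of less than 3 months", those scoring below 15 on the MMS-E and those not living at home, so its own mortality may be lower; hence the 10 to 15% rows. The between-arm contrasts have no basis in the article. Overstatement common to both arms largely cancels in an incremental comparison. The lost differences are also small beside sampling error: with an assumed QALY SD of 0.2 to 0.3 and 80 per arm, the standard error is SD × √(2/80), or 0.032 to 0.047. All of this stands, and it limits the weight of the point. A systematic error with a known correction is still worth removing.

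**Conclusion.** The point holds as a defect in a stated rule, not as a complaint about missing detail. One unrestricted carry-forward rule sits beside a planned cost-QALY analysis in a condition with substantial cited mortality, and following the rule literally gives a wrong number.

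It overstates mean QALYs by about 0.05 to 0.08 per patient at the background 25% mortality, and by about 0.02 to 0.05 at an assumed 10 to 15%, in both cases with a constant hazard and an assumed flat utility of 0.4 to 0.6. It removes most of any survival-driven QALY difference (about three quarters under the recovering profile tried here), and all of it if utility is flat.

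The weight is minor to moderate: the aim is secondary, and the application of the rule to QALYs is the literal reading, not an explicit statement.

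**What to change.** Amend the carry-forward sentence in the data analysis section:

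1. State that death is not missing data and that no value is carried forward past it.
2. For QALYs, set utility to 0 from the date of death and compute the area under the utility curve to death or 12 months, whichever comes first.
3. Impute only the missing questionnaires of survivors, by multiple imputation instead of carry-forward.

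A cross-reference where the EQ-5D-5L is described would tie the two sections together.

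The cost is a few sentences and a little programming. The date of death should be recorded with the mortality already registered, since the article does not mention dates. No extra patients or visits are needed.
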